#### Motor Skills

Global motor skills were evaluated with 3 tests issued from the Eurofit Test Battery [38,39] because it is valid and reproducible for school children aged 6-18 [40]. They were implemented as described in the Eurofit Handbook [38]. Cardiorespiratory fitness was also measured with the PREFIT 20-m Shuttle Run Test, an adaptation of the original 20-m Shuttle Run Test for children [41]. These tests were carried out at T1, T2, T3, T4, and T5.

##### Standing Broad Jump

This test is included in the Eurofit Test Battery and measures the explosive power of the legs and intersegmental coordination [38].

##### Platte Tapping Test

This test is included in the Eurofit Test Battery [38]. It measures the speed and coordination of the upper limb.

##### 6 × 5-m Shuttle Run

This test was adapted from the 10 × 5-m Shuttle Test of the Eurofit Test Battery [38]. It measures running speed and agility.

##### Cardiorespiratory Fitness: PREFIT 20-m Shuttle Run Test

The aerobic capacity was measured with an adapted version of the original 20-m Shuttle Run Test [42]: the PREFIT 20-m Shuttle Run Test, more appropriate for young children [41]. Children had to run back and forth between 2 lines 20 m apart with an audio signal giving the rhythm of the corresponding speed. The running speed increased by 0.5 km/h each minute. Some adaptations of the original test were made to fit children’s capacities by decreasing the initial speed (ie, 6.5 km/h instead of the original 8.5 km/h) and by having 2 evaluators running with a reduced group of children (eg, 8-12 of the same age) in order to provide an adequate pace. The test ended when the child failed to reach the end lines concurrent with the audio signal on 2 consecutive occasions or when the child stopped because of exhaustion. The results were expressed as the number of laps completed. From this value, the maximal aerobic shuttle running speed (km/h) and the maximal oxygen uptake (VO_2max_ mL/kg/min) can be calculated.

#### Attentional Capacities

The computer-based modified Erickson Flanker Task was used as a variant version of the Flanker-Task [43,44]. It was designed with the software SuperLab 4.5 (Cedrus Corporation). It permits the measurement of inhibition and cognitive flexibility, which are identified as attentional capacities [45]. Inhibition refers to focusing on essential elements of the environment while not focusing on disturbing elements, and cognitive flexibility involves changing from one cognitive operation to another. The sustained attention was evaluated as well. The task was to respond to a target stimulus while ignoring distracting stimuli presented on a 15-in. computer screen. In this version the stimuli were pictograms of a fish oriented either toward the left or toward the right. The child was instructed to press on the “P” key of the keyboard (located on the right hand side) with the right hand for target fishes facing to the right, and on the “A” key of the keyboard (located on the left hand side) with the left hand for target fishes facing to the left. The test included 3 conditions: (1) standard flanker, (2) reverse flanker, and (3) mixed condition. In the standard flanker condition, the fishes were blue. The target stimulus was the fish located in the middle of the screen. It could be oriented to the left or to the right and could be accompanied on either side by other fishes facing either direction and they had to be ignored (ie, distractors). In the reverse flanker condition, the fishes were pink. In contrast to the previous condition, the target stimuli were the fishes located on either side of the screen while the middle fish had to be ignored (ie, the distractor). These 2 conditions require sustained attention to remember the initial instruction and stay focused throughout the test, and inhibition of the appropriate distractor. In the mixed condition, trials from the standard condition (with blue fishes) and trials from the reverse condition (with pink fishes) were randomly mixed up. The child had to adapt to the variation of the rule to be applied. Thus, this condition required cognitive flexibility on top of sustained attention and inhibition.

For each condition, after being instructed in the task, the child practiced with 2 familiarization blocks of 7 stimuli: 1 block with feedback on the correctness of his/her answer and 1 block without feedback. If necessary, these blocks were repeated until it was made sure that the task was clearly understood. The child was asked to respond as quickly and as accurately as possible by pressing on the appropriate key (“P” or “A”) according to the stimulus [44].

The reaction time and the correctness of the answers were recorded to measure sustained attention, inhibition, and flexibility. This test was carried out at each measurement period (T1, T2, T3, T4, and T5), only for children in grades 2, 3, and 4. Children were assessed during school morning from 8:30 to 12:00. The measurements took place in a separate classroom and 1-4 children were assessed at the same time. Each child was placed in a corner of the classroom in front of a 15-in. screen, with the attendance of 1 specialist researcher. The instructions were given verbally and individually by the specialist.

#### Academic Achievement

Measures of academic achievement for each child and for both schools were collected at the beginning of each academic year, that is, at baseline (T1), follow-up assessment (T3), and final assessment (T5). Criteria of assessment of the academic achievement were the same for both schools. These data were provided by the local educational services. Percentages of success for “reading,” “spelling,” “arithmetic,” and “mathematics” were collected.

#### Questionnaire

In addition to collecting academic achievement data, a questionnaire was distributed at the beginning of each school academic year (ie, T1, T3, and T5). Parents were asked to complete a questionnaire in order to obtain (1) sociodemographic information (age and gender of the child, socioeconomic data measured by the 4-item scale “Family Affluence Scale II” [FAS II] [46], marital status, and level of qualification of the parents) and (2) subjective information related to children’s PA and ST behavior (number of sports and outdoor activities practiced, parental perception of the competence of their children in PA practice, sedentary behavior of the child [time spent playing video games, watching television, and artistic and musical activities]).

### Statistical Analysis

STATISTICA version 12.5 (StatSoft/Dell) for Windows and R software will be used. Descriptive statistics of MVPA and ST for the whole day and within the different specific periods of the day will be calculated for both schools at the different assessment times. To examine the effectiveness of the intervention to promote PA and reduce ST, ANOVAs contrasting 2 schools × 5 assessment times with repeated measurement on the last factor will be used on MVPA and ST. Furthermore, chi-square analysis will be carried out to compare the number of children between experimental and control groups who comply with MVPA recommendations for the overall day and during school time.

To explore the longitudinal relationship between PA, motor skills, attention, and academic achievement, multiple regression analyses will be conducted to determine which variables will predict academic achievement scores [47]. We will attempt to examine whether PA or motor variables predict academic achievement through attention. As there are many variables in each category, a principal component analysis will be used to select the variables that are most correlated. Finally, the decision tree process will be used to examine more accurately the longitudinal relationships between the variables selected.

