### Study Design and Population

The study was designed as a randomized controlled trial with 2 arms. In a mid-sized city in the southern part of France, 2 primary schools located in the city’s disadvantaged neighborhood were invited to participate in the study. In France, neighborhoods are classified as disadvantaged on the criterion of income per inhabitant: this income is compared with the average income of the city and that of France. This defines the unfavorable social and economic conditions of the neighborhood and its inhabitants. For example, in the neighborhood considered in this study, the unemployment rate is the highest in the city (26% vs 18%) as well as the prevalence of social housing (49% vs 23%).

Both primary schools agreed to participate in the project. They included children from grade 1 (6 years old) to grade 5 (10 years old) and had never benefited from any intervention in the field of PA. Schools were randomly assigned to either experimental (School A) or control group (School B; see Figure 1). Because the intervention is school based, all the children were included in the study (n=141 for school A and n=148 for school B). Based on studies already published on the same theme, the effects of the intervention are expected to be moderate (standard difference≈0.32, equivalent to an average change in MVPA measurement of 8 minutes per day; SD 18 minutes). In addition, in order to detect a difference of 0.32 with a statistical power of 0.8, a significance level of .05, and a retention rate of approximately 91% with a pre/post comparison, the number of participants should be 70. As a precaution, more children were included. Thus, the number of children enrolled was above the minimum required.

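### The trial is sized on a pre/post comparison of MVPA, but effectiveness rests on unranked tests led by an undirected five-wave ANOVA

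*Protocol article*

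**What the plan says.** The sample-size text in Study Design and Population rests on MVPA alone: "standard difference≈0.32, equivalent to an average change in MVPA measurement of 8 minutes per day; SD 18 minutes". It gives "a statistical power of 0.8" and "a significance level of .05", and then "a retention rate of approximately 91% with a pre/post comparison, the number of participants should be 70".

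Statistical Analysis gives a different set of tests for the effectiveness question: "ANOVAs contrasting 2 schools × 5 assessment times with repeated measurement on the last factor will be used on MVPA and ST". It then adds chi-square tests to "compare the number of children between experimental and control groups who comply with MVPA recommendations for the overall day and during school time", without naming an assessment time.

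The Aims section joins promoting PA and reducing ST in one objective and ranks neither. Study Design and Population places T1 and T2 in 2016/2017, before the programme. T3 and T4 fall in the intervention year 2017/2018. T5 is in June 2019, after a year without intervention.

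**The concern.** The test that was sized and the tests that will be run are not the same. The sizing names one outcome and a before/after comparison. The analysis names two outcomes, five waves and two compliance proportions, and does not say which result decides.

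The interaction in a 2 × 5 ANOVA asks whether the between-school difference is constant over all five waves. That is not the same as asking whether the programme worked. Two of the five waves precede it and one follows a year after it ended. A school difference that shifts between T1 and T2, or appears only at T5, can make the interaction significant and be read as an effect of the programme. With no ranking, a reader also cannot tell whether a significant result on ST or on compliance alone would count as success.

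**Working it through.** **1. The stated 70.** Inputs: d = 0.32, power 0.8, level .05, retention 91%, all from Study Design and Population. Sidedness is not stated. For a paired pre/post comparison, n = ((z_α + z_power)/d)².
- One-sided: ((1.645 + 0.842)/0.32)² = 60.4, so 61; 61/0.91 = 67.03, so 68 (69 with the t distribution). This is close to 70.
- Two-sided: ((1.960 + 0.842)/0.32)² = 76.6, so 77; 77/0.91 = 84.6, so 85. This does not match.

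Other routes also land near 70. A two-school, two-wave interaction with f = 0.16 gives 71 if a correlation of 0.6 is assumed. The figure therefore does not settle which formula was used, but the text describes a pre/post comparison, not five waves.

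The stated effect is also not unique: 8/18 = 0.444, whereas 0.32 × 18 = 5.76 minutes. Both 5.76 and 8 minutes are carried below.

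**2. Power of the planned interaction against a directed contrast.** Inputs: Table 1 accelerometry at T4, 45 in School A and 51 in School B. These are the most children who could have all five waves, which a standard repeated-measures ANOVA requires. SD is 18. Assumed: equal correlation ρ between waves, an effect δ at T4 only, children treated as independent, two-sided .05.

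For the interaction F, λ = [δ²(1 − 1/5)/(σ²(1 − ρ))] × n₁n₂/(n₁ + n₂). With ρ = 0.5 and δ = 5.76: λ = (33.18 × 0.8/162) × (45 × 51/96) = 3.92 on 4 and 376 df, giving power 31%.

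For T4 minus the mean of T1 and T2, SD = 18√((1 − 0.5)(1 + 1/2)) = 15.59. SE = 15.59√(1/45 + 1/51) = 3.19, and 5.76/3.19 = 1.81 on 94 df, giving power 43%.

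For T4 minus T2 only, SD = 18√(2 × 0.5) = 18. SE = 3.68, and 5.76/3.68 = 1.56, giving power 34%.

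| ρ | δ (min) | 2 × 5 interaction F | T4 vs mean of T1, T2 | T4 vs T2 |
|---|---|---|---|---|
| 0.3 | 5.76 | 23% | 33% | 26% |
| 0.5 | 5.76 | 31% | 43% | 34% |
| 0.7 | 5.76 | 50% | 64% | 52% |
| 0.3 | 8 | 42% | 56% | 44% |
| 0.5 | 8 | 57% | 70% | 58% |
| 0.7 | 8 | 82% | 89% | 79% |

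The gain in power comes from averaging the two pre-intervention waves. T2 alone gives about the same power as the F test, and its advantage is that it asks the right question.

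**3. Waves outside the programme.** Under equal correlation, λ does not depend on which wave deviates. An 8-minute school difference confined to T1 would therefore make the interaction significant as often as one confined to T4: 42%, 57% or 82% for ρ = 0.3, 0.5 or 0.7. The same holds for T5.

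**4. Chance of a false claim.** This assumes each test is done at .05 and any one significant result is taken as effectiveness.
- Two ANOVAs, independent: 1 − 0.95² = 9.75%.
- Four tests (two ANOVAs and two chi-squares, each once), independent: 1 − 0.95⁴ = 18.5%.
- Four tests simulated with correlated outcomes (assumed MVPA-ST correlation 0 to −0.8, day-school MVPA correlation 0.3 to 0.7): about 16-19%.
- MVPA alone decides, or MVPA and ST must both succeed: no inflation above 5%.

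**The case against.** The article is condensed. Multiplicity control, follow-up contrasts after an omnibus test and the wave used for a chi-square are details that a full protocol or SAP may hold. Using all waves is a legitimate longitudinal design, and T3 and T4 repeat the seasons of T1 and T2 on purpose. Sizing on a simplified comparison is common. MVPA is the only sized outcome and could be read as primary in practice, and the compliance tests are introduced as an addition.

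Most of this stands against a stronger reading that a reader might infer: that every test is run at .05 and the trial's false-positive rate far exceeds 5%. The documents do not support it. Statistical Analysis gives no level; .05 appears only in the sample-size sentence. No rule says that one significant result is enough. Rates of 34% (eight tests) or 46% (twelve) would need the chi-squares repeated over three or five waves, which the article does not describe. The twelve-test count also includes waves before the programme, where a difference could not be a claim of effect.

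The objection does not remove the mismatch. The article states the test it will run, and that test is neither the comparison it sized nor one aimed at the intervention period. Treating MVPA as primary does not repair this, because the five-wave interaction on MVPA would still respond to T1, T2 and T5.

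**Conclusion.** The point holds in a limited form and should be acted on. The planned interaction does not isolate the pre/post MVPA comparison on which the trial was sized, and the effectiveness results are not ranked. For an effect at T4 only, the interaction has 23-50% power at 5.76 minutes and 42-82% at 8 minutes. T4 against the mean of T1 and T2 has 33-64% and 56-89%. These figures rest on the T4 counts, SD 18, equal correlations of 0.3 to 0.7 and independence between children. Having one school per arm is a separate matter and is not counted here.

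The inflation of the error rate is conditional: about 16-19% if any one of four results at .05 may be claimed, and none under the two stricter rules above.

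**What to change.** Name whole-day MVPA, the outcome already sized, as primary. Test it with one contrast: the between-school difference in change from the pre-intervention waves to T4. The article labels both T1 and T2 as baseline, so state which is meant: either their mean, or T2, which matches T4 by season. Make that choice before the school comparison is seen. Use all children with data at the waves concerned, so that five complete waves are not required. Report ST, T5 and the two compliance proportions as secondary, either Holm-adjusted or labelled supportive.

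The change needs a short rewrite and no new data, but it has costs. The secondary outcomes lose stand-alone status. T4 has the lowest accelerometry coverage of the five waves (45/137 and 51/154), so the power of this contrast must be restated and cannot be taken as the planned 0.8. The article says the analyses are close to completion. If outcome data by school have already been seen, the choice must be reported as made after data collection.

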## Introduction

### Background

Physical inactivity has been recognized in the last decade as a major cause of noncommunicable disease, being held responsible for more than 5.3 million of the 57 million deaths that occurred worldwide in 2008, and for a decrease in life expectancy [1]. Furthermore, physical activity (PA) has a protective effect against more than 20 chronic diseases, including obesity [2]. Thus, the World Health Organization (WHO) has set a global action plan to increase PA levels and decrease sedentary time (ST), with the aim of “a 15% relative reduction in the global prevalence of physical inactivity in adults and in adolescents by 2030” [3]. To reach that goal, primary school children are an important target because behaviors adopted in childhood affect health habits and lifestyle choices in adulthood [4,5]. International guidelines for 6-11-year-old children recommend at least 60 minutes of moderate-to-vigorous PA (MVPA) per day as well as a reduction of sedentary behavior [3]. However, data suggest that when conservative cut points are used to define MVPA, less than half of the children meet the 60-minute MVPA recommendation [6,7]. As an example, the IDEFICS study reported an average MVPA of 49 minutes for boys and 36 minutes for girls and an average ST of 370 minutes in 8-year-old children from 8 European countries [8]. Furthermore, children of low socioeconomic status seem to have lower PA levels as well as higher ST [9]. Thus, they should be specific targets for intervention because the WHO defines the reduction of inequalities as one of its Sustainable Development Goals [3].

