As stated by the WHO, if PA has to be increased, ST also has to be reduced, and healthy PA habits should be learned during childhood [3-5]. In fact, if 7-year-old children spend about half of their waking time in sedentary behavior, this proportion increases up to around 75% at 15 years of age [21]. Furthermore, the effects of physical inactivity and sedentary lifestyle are independent of health, especially at the cardiometabolic level [22]. Thus, specific interventions to reduce ST are needed. Usually, these interventions focus on the development of classroom material. A literature review analyzed 13 studies and showed that height-adjustable desks decreased sitting time in the classroom [23]. Active classroom lessons are also used in several intervention programs to promote PA and break down ST, leading to improvement in on-task behavior during academic instruction [24]. In order to show evidence of the hypothesized change of behavior, an objective method of measurement of PA and ST, such as accelerometry, in preintervention and postintervention periods is necessary because self-reported ST is highly underestimated [25].

To help convince the educational authorities as well as the teachers to implement such interventions, recent evidence underlines the role of physical movement in the establishment of fundamental mental processes during childhood and adolescence, leading to cognitive benefits [26,27]. PA seems to have positive effects on the attentional capacities of children as well as academic achievement [28]. In fact, physical condition would be a mediatory element between PA and executive functions that include attentional capacities [29]. In addition, the development of gross and fine motor skills has a positive impact on cognitive capacities [30]. Thus, it is necessary to explore the relationships between PA, motors skills, attentional capacities, and academic achievement for children with low socioeconomic status.

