#### Principal Outcomes From Measurements at Baseline Concerning PA and ST

On average, children aged 8-10 spent 67.20 (SD 17.83) minutes in MVPA and 602.97 (SD 36.32) minutes in ST on weekdays. At different periods of the school day, it appeared that (1) during school time, the international recommendation to spend 30 minutes in MVPA were fulfilled by only 26.92% of the grade 2 children and 5.40% of the grade 5 children. In fact, children spent 22-27 minutes in MVPA during school time while they were sedentary for 260-270 minutes. Thus, it was confirmed that school is a highly sedentary place where PA has to be promoted during recess and also during class time through sedentary breaks and active learning strategies. (2) During lunch time, sedentary activities represented 80% of the period (ie, 88-93 minutes of ST against 10-13 minutes of MVPA), suggesting that this period of the school day could be used for children to be more active and less sedentary through an organizational process. (3) Before school, only 2-3 minutes were spent in MVPA while 22 minutes were ST, suggesting that active transportation to school was scarce or that school is very close to home for some children. Thus, children’s and parents’ sensitization to active transportation should be developed.

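### The compliance chi-square compares the two schools without sex or grade, although the trial's own baseline shows a five-fold grade gradient in that outcome

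*Protocol article*

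**What the plan says.** Under Statistical Analysis, the protocol article names two analyses of effectiveness. The first is "ANOVAs contrasting 2 schools × 5 assessment times with repeated measurement on the last factor will be used on MVPA and ST". The second is that "chi-square analysis will be carried out to compare the number of children between experimental and control groups who comply with MVPA recommendations", for the whole day and for school time. School and, in the ANOVA, time are the only factors named.

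Elsewhere the article shows that sex and grade matter:

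- The baseline results report that the 30-minute school-time recommendation was "fulfilled by only 26.92% of the grade 2 children and 5.40% of the grade 5 children". These are trial data.
- The Background cites a European study of 8-year-olds with "an average MVPA of 49 minutes for boys and 36 minutes for girls". These are not trial data, and the trial's own baseline MVPA is not split by sex.

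The parent questionnaire collects "sociodemographic information (age and gender of the child". Table 1 shows it returned for between 32.6% and 67.3% of pupils, depending on school and wave.

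**The concern.** One school was allocated to each arm, so nothing balances sex or grade between arms at child level. Compliance can be judged only for children with accelerometer data, and Table 1 shows that this group changes. From T2 to T4 to T5 the counts run 96, 45, 71 in School A and 116, 51, 86 in School B. At least 71 − 45 = 26 and 86 − 51 = 35 of the T5 wearers therefore had no T4 measurement.

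A chi-square at any one wave compares different children across schools and makes no use of their earlier values. If the wearers in one school are younger or include more boys, that difference enters the compliance comparison directly and would be read as an intervention effect, or would offset one. The article says that analyses are close to completion, so the wording can be corrected before results are reported.

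**Working it through.** **Yardstick.** The plan gives no figure for this point. The effect sought is stated as "standard difference≈0.32, equivalent to an average change in MVPA measurement of 8 minutes per day; SD 18 minutes". Those figures do not agree with each other (8/18 = 0.44, not 0.32). That is a separate matter; only the 8 min is used here.

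**1. Grade and school-time compliance (trial data).** The gap is 26.92 − 5.40 = 21.52 points, a ratio of 26.92/5.40 ≈ 5. Shift in compliance = gap × between-school difference in the mix of grades 2 and 5:

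- 10 points: 0.10 × 21.52 = 2.2 points
- 20 points: 0.20 × 21.52 = 4.3 points
- 30 points: 0.30 × 21.52 = 6.5 points

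This contrasts two widely separated grades. If compliance falls steadily with grade, shifts between neighbouring grades would move it less.

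**2. Sex and MVPA (assumes that the cited gap applies here).** The gap is 49 − 36 = 13 min. A 20-point difference in the share of boys gives 0.20 × 13 = 2.6 min, and 2.6/8 = 0.33 of the effect sought. Sex alone reaches 8 min only at 8/13 = 0.62, a 62-point imbalance.

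**3. Sex and whole-day compliance (same assumption, plus normal MVPA and equal numbers of boys and girls).** The baseline mean is 67.20 and the SD 17.83, so the within-sex SD is √(17.83² − 6.5²) = 16.60.

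- Boys (mean 73.7) reaching 60 min: 80%
- Girls (mean 60.7) reaching 60 min: 52%
- Difference: about 28 points, so a 20-point sex imbalance moves compliance by 0.20 × 28 = 5.6 points
- An 8-min rise from 67.2 to 75.2 with SD 17.83: 66% to 80%, about 15 points

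The imbalance would be worth a little over a third of what an 8-min effect produces (5.6/15 = 0.37).

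**4. Does the ANOVA share the problem?** This was simulated with no intervention effect, a constant 13-min sex gap, 45 and 51 children (the T4 counts), and half of the within-sex variance lying between children:

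| Boys, A vs B | Change in the same children: bias; rejections | One-wave comparison: bias; rejections |
|---|---|---|
| 50% vs 50% | 0.0 min; 4.2% | 0.1 min; 4.4% |
| 60% vs 50% | 0.0 min; 5.0% | 1.3 min; 6.9% |
| 70% vs 50% | 0.1 min; 4.6% | 2.6 min; 10.8% |
| 80% vs 40% | −0.1 min; 5.3% | 5.2 min; 30% |

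The within-child comparison is unaffected. The one-wave comparison, which is the structure of the chi-square, is not.

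**The case against.** **The repeated-measures ANOVA compares each child with itself.** This stands. A constant sex or grade difference drops out of school × time among children measured at all waves. What remains exposed is the school main effect, time trends that differ by sex or grade, and any analysis of a changing set of wearers.

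**Chance imbalance is already in the unadjusted standard error.** This also stands. At T4 the SD of the difference in the share of boys is √(0.25/45 + 0.25/51) = 0.102, or 1.33 min. That is part of the total standard error of 17.83 × √(1/45 + 1/51) = 3.65 min. Chance mix therefore does not raise the overall type I error; a systematic difference between the schools does. None is shown: the sex and grade mix of wearers is not reported, both schools cover grades 1 to 5, and wear at T4 was almost equal (32.8% and 33.1%). Equal rates do not establish equal mix, but they are no evidence of a difference.

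**Covariates are commonly left to the analysis plan.** This is fair in general and limits how strongly the point can be put. But the article names the test, and a plain chi-square has no place for covariates.

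**The questionnaire need not be the only source.** This stands in part. Grade is evidently known, since results are reported by grade. Sex does not change, so one return at any wave is enough, and the per-wave rates understate coverage.

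**Stronger readings.** A reader might infer from 13 min exceeding 8 min that a change in wearers could mimic or hide the whole effect. The documents do not support that: the bias is the gap times the imbalance, and 62 points would be needed. A reader might also derive a per-grade drift in ST from the cited rise in sedentary share ("this proportion increases up to around 75% at 15 years of age", from about half at age 7). The trial's own 602.97 min is already 77% of an assumed 13-hour day (602.97/780), so that trajectory does not describe this trial's ST measure.

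**Conclusion.** The point holds in a limited form. The compliance chi-square is open to bias from differences in grade and sex mix, with one school per arm and a changing set of wearers. For grade the size rests on trial data: about 4.3 points of school-time compliance per 20-point difference in the mix of grades 2 and 5. The denominators behind the two percentages are not given, so their precision is unknown. For sex the size (2.6 min of MVPA, or about 5.6 points of whole-day compliance, per 20-point imbalance) depends on a cited external gap and, for compliance, on normality.

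The school × time term is not affected by constant differences in the children that it retains. This is a foreseeable, unguarded and partial distortion; the documents do not show that one occurred.

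**What to change.** - Replace the chi-square by a logistic model of compliance with school, sex and grade.
- Add sex and baseline grade to the MVPA and ST model. Limit time interactions to what the number of wearers supports. All five grades and sex, each crossed with five waves, would take (1 + 4) × 5 = 25 degrees of freedom. The three starting grades that can normally reach T5 would take (1 + 2) × 5 = 15. At most 45 and 51 children can have all five waves.
- Take sex and grade from school records where the parent questionnaire was not returned. Local educational services already supply pupil-level achievement data.
- Report the sex and grade mix of wearers by school and wave, so that readers can see whether an imbalance arose.

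The cost is some degrees of freedom, one data request and revised wording. The change deals with child-level mix only; it does not separate the intervention from other differences between two single schools.
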